## Methods/Design

### Study design and objectives

This is a prospective pagoda (community)-based cohort study with the following primary objectives: (i) to determine the seroprevalence of antibodies indicating previous *Aedes*-transmitted DENV infection in children; and (ii) to describe the seropositivity to *Aedes* salivary gland homogenate (Table 1). The study will screen up to 1200 and recruit up to 771 children aged 2–9 years for study enrollment and then follow them longitudinally for three years. The study is being conducted over three years given the high rate of variability in *Aedes*-transmitted disease transmission from year to year. The study is focused on children aged 2–9 years of age as they have the greatest burden of disease in Cambodia and thus offers comparability to other pediatric DENV cohorts [23–25, 27].

**Table 1 Tab1:** Study objectives and endpoints

Objectives	Endpoints	Justification for endpoints
• Primary		
Describe the seroprevalence of dengue infection (both symptomatic and inapparent) in children aged 2–9 years-old in Kampong Speu	Prevalence of symptomatic and inapparent dengue infection (serotypes 1–4) as detected semiannually *via* ELISA (binary outcome present/absent) over a 3-year period in Kampong Speu in children aged 2–9 years-old	Detailed knowledge of dengue seroprevalence and transmission season variability will help establish an epidemiological foundation to prepare for larger future studies such as disease incidence studies or vector interventional trials
Describe the seroprevalence of reactivity to *Ae. aegypti* salivary gland proteins in children aged 2–9 years-old in Kampong Speu	Prevalence of *Ae. aegypti* salivary gland homogenate reactivity as detected by ELISA assay (binary outcome present/absent) during wet and dry seasons over a 3-year period in Kampong Speu in children aged 2–9 years-old	Characterizing the *Ae. aegypti* salivary protein reactivity profile in Cambodians is the first step prior to assessing how *Ae. aegypti* saliva exposure modulates disease in humans
• Secondary		

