Demographics	×									
Baseline medical history questionnaire	×									
Baseline physical exam	×									
Interval exam and questionnaire		×	×	×	×	×	×			
Concomitant medication review	×	×	×	×	×	×	×	×	×	×
Sick visit exam (with height and weight) and questionnaire								×		
Convalescent exam and questionnaire									×	×
Height and weight	×						×	×		
Vital signs	×	×	×	×	×	×	×	×	×	×
Dengue rapid diagnostic test (RDT)								×		
RT-PCR multiplex for acute arboviral diagnosis								× (if RDT+)		
Sera collection for ELISAs	×	×	×	×	×	×	×	× (if RDT+)	×	
Hemoglobin		×								
Alpha-thalassemia screening		×								
Peripheral blood mononuclear cells	×						×	× (if RDT+)		×
Complete case report forms	×	×	×	×	×	×	×	×	×	×

*Note*: Dry seasons visits take place every March whereas wet season visit take place every August

To reduce bias from loss to follow-up, the study team enrolls volunteers who are located within 5.5 km of the district hospital, will do follow-up sampling in the community, and will provide incentives commensurate with the previous studies approved by the Cambodian ethics committee.

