### Statistical analysis

The primary endpoints will be defined as:(i)Seropositivity to DENV1-4 per indirect IgG ELISA (with plaque reduction neutralization assays performed as necessary to confirm inapparent dengue infections)(ii)Seropositivity to *Ae. aegypti* salivary gland homogenate

Seroprevalence to each dengue serotype will be presented as a proportion for each timepoint. Unadjusted and adjusted logistic regression models will be performed evaluating the relationship between time and seroprevalence, with adjustments for age, year or season of collection, and socio-economic conditions (e.g. type of housing). Further, the seroconversion rate and change in the immune status will be determined by participants and separated by age group during the study period. Quasi-Poisson regression models will be fit to evaluate the relationship of age, year, socio-economic conditions (e.g. type of housing) to the primary endpoints of dengue infection or *Ae. aegypti* salivary gland homogenate seropositivity and to estimate prevalence ratios.

Because seroconversion to *Ae. aegypti* salivary gland homogenate is measured repeatedly on subjects over three years during wet and dry season, a single subject may be negative for seroconversion at one time, and positive at a later time. This will allow us to perform our secondary objective to evaluate the kinetics of the antibody response. Given these changing values, seroprevalence to *Ae. aegypti* salivary gland homogenate will be presented as proportion representing point prevalence for each season in each year of the study.

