Exploratory analyses for the relationship of *Ae. aegypti* saliva seroconversion with disease development will model the rate of incidence of composite *Aedes*-transmitted arboviral disease (as defined above) using a quasi-Poisson model. The primary interest will be in the relative risk (RR) of infection comparing at risk subjects with seroconversion to *Ae. aegypti* salivary protein to those without seroconversion at that time. Exposed will be defined as those with seroconversion to specific *Ae. aegypti* salivary protein while unexposed will be those without reactivity at baseline and each follow-up time point. For this analysis, seroconversion will be defined as a binary variable (present/absent) based on the level of antibody to *Ae. aegypti* salivary gland homogenate (positivity is generally considered two standard deviations above the mean optical density value for negative controls as determined by an ELISA assay with further adjustment as needed to account for cross-reactivity to *Anopheles* or *Culex* saliva).

To compare the rates in secondary/exploratory outcomes for significant differences in arboviral infection between participants with or without evidence of salivary protein exposures or to examine other groups such as alpha thalassemia variants, we will use quasi-Poisson models and central Fisher’s exact tests. As previously stated, secondary and exploratory analyses will evaluate ELISA values as background (negative), low, medium and high quartiles, based on range and as a continuous variable. From the subset of samples with the highest positive values from both primary and secondary analyses, Western blot assays will be used to identify the most immunodominant protein candidates for functional characterization and future studies on epitope identification and characterization. Western blot assays will also be run against *Culex* and *Anopheles* saliva to account for cross-reactive immunogenicity to mosquito saliva in general.

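### The prevalence-ratio model for saliva seropositivity has year but no season, so if the enrolment round is pooled with the six seasonal visits the year ratio can show a change that did not occur.

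*Protocol article*

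**What the plan says.** In the protocol article, Statistical analysis, quasi-Poisson models will be fitted "to evaluate the relationship of age, year, socio-economic conditions (e.g. type of housing) to the primary endpoints of dengue infection or" saliva seropositivity. The sentence ends "salivary gland homogenate seropositivity and to estimate prevalence ratios", so this is the model that produces prevalence ratios for a primary endpoint. Its listed covariates are age, year and socio-economic conditions.

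The same section treats season differently in two other places. The logistic models are run "with adjustments for age, year or season of collection, and socio-economic conditions (e.g. type of housing"). Saliva seroprevalence, because a child's status can change between visits, is "presented as proportion representing point prevalence for each season in each year of the study".

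The schedule is in Table 2 (Study design and objectives). Its note says: "Dry seasons visits take place every March whereas wet season visit take place every August". The row "Sera collection for ELISAs" is marked at enrolment and at all six seasonal visits, in the order dry, wet, dry, wet, dry, wet.

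**The concern.** The article gives its own reasons to expect saliva seropositivity to vary with season. Table 1 says saliva IgG may persist 30–40 days, possibly up to 4 months, which is shorter than the roughly five months from March to August. It links season to vector abundance and makes wet versus dry season part of a secondary endpoint. The Background puts the dengue transmission peak between July and November.

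A year term without season is harmless when every year contains the same mix of wet and dry rounds. Seven rounds cannot be split into years that each hold equal numbers of wet and dry rounds. If all seven are pooled, some year differs in its mix, and its ratio compares seasons as well as years. What is at stake is the modelled year-to-year ratio for saliva seropositivity: it could suggest a change in exposure when wet and dry prevalence have both stayed constant.

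**Working it through.** **The plan's own figure.** The article gives no figure for a year or season effect. Its only size figure is 701 evaluable children (701 × 1.10 = 771 enrolled), set for dengue seroprevalence. It is used below only as the simulation sample size.

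**Inputs from the article.** Covariates: age, year, socio-economic conditions. Rounds: enrolment, then dry, wet, dry, wet, dry, wet.

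**Inputs assumed.** Wet prevalence w and dry prevalence d, constant over the whole study. The article gives neither, and its Sample size calculation section says such presumptions are difficult. Enrolment season and the definition of year are also not stated, so several are tried.

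**Formulas.** With no season term, each year's expected prevalence is the mean of its rounds.

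- Calendar years, wet enrolment alone in year 1: ratio = ((w + d)/2) / w.
- Wet enrolment grouped with the first dry and wet visits: ratio = ((w + d)/2) / ((2w + d)/3).
- 12-month years from wet enrolment, final wet visit counted in year 3: years 1 and 2 are both (w + d)/2; year 3 is (2w + d)/3.
- Enrolment left out: every year is (w + d)/2, ratio 1.00.

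**At w = 0.60, d = 0.40.**

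- Calendar: 0.50/0.60 = 0.83 for every later year.
- Grouped: 0.50/(1.60/3) = 0.50/0.533 = 0.94.
- 12-month: year 2 is 0.50/0.50 = 1.00; year 3 is 0.533/0.50 = 1.07.

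**Other gaps and codings** (ratio to year 1, no true change):

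| Placement of rounds | 60%/40% | 50%/30% | 30%/25% |
|---|---|---|---|
| Calendar years, wet enrolment alone in year 1 | 0.83 | 0.80 | 0.92 |
| Wet enrolment grouped with first dry and wet visits | 0.94 | 0.92 | 0.97 |
| 12-month years from wet enrolment, last wet visit in year 3 | 1.00, then 1.07 | 1.00, then 1.08 | 1.00, then 1.03 |
| As above, last wet visit alone in year 4 (year 4 ratio) | 1.20 | 1.25 | 1.09 |
| Dry enrolment grouped with first dry and wet visits | 1.07 | 1.09 | 1.03 |
| Dry enrolment alone in the preceding calendar year | 1.25 | 1.33 | 1.10 |
| Enrolment left out | 1.00 | 1.00 | 1.00 |

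With w = d every entry is 1.00.

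**Simulation.** 701 children, a child-level random effect with SD 1 on the logit scale, Poisson regression with Pearson scale, year categorical, 200 replicates, no true change. Year 2 against year 1, wet enrolment:

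| Wet/dry and coding | Ratio without season | p < 0.05 | Ratio with season | p < 0.05 |
|---|---|---|---|---|
| 50%/30%, calendar | 0.81 | 100% | 1.005 | 1.5% |
| 50%/30%, grouped | 0.93 | 46% | 1.006 | 3% |
| 30%/25%, calendar | 0.92 | 18% | 1.003 | 2.5% |
| 30%/25%, grouped | 0.97 | 6.5% | 0.995 | 4% |

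Adding season removes the artefact in each case.

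**The case against.** **The imbalance comes only from enrolment, and the article does not say that enrolment enters this model.** This is correct. Clinical and laboratory procedures describes baseline serum for dengue antibodies only, and Table 1 ties the saliva endpoint to wet and dry seasons. Against that, Table 2 marks ELISA serum at enrolment, and the exploratory analysis defines the unexposed as "those without reactivity at baseline and each follow-up time point", so baseline saliva status is expected to exist. Nothing excludes it from the prevalence-ratio model. The point is therefore conditional on its inclusion.

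**A reader might infer a false fall that affects every year ratio equally.** The article does not support this. The pattern needs wet enrolment together with calendar years, or with enrolment grouped into the first year. Wet enrolment is plausible: registration was on 23 May 2018, the first follow-up is dry, and the plan is to recruit children and "then follow them longitudinally for three years", ending at a wet visit. It is still an inference, since the article states only a three-month enrolment period. With 12-month years from a wet enrolment, year 2 is unbiased and a later year shows a rise. Dry enrolment also gives a rise.

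**A reader might also infer that the three-year duration rests on this year ratio.** It does not. The reason given is year-to-year variability in disease transmission, not in saliva exposure.

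**Season is handled elsewhere.** This is partly true. The season-by-year point prevalences already allow August-to-August and March-to-March comparison. The logistic models offer year or season, and further models use rainfall, temperature and humidity. None of these puts season into the model that yields the prevalence ratios.

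**A condensed article may leave model detail to a fuller document.** That is fair for the coding of year and the place of enrolment, which are not counted as faults here. The covariate list itself is stated, and season is absent from it while present in the logistic list just before.

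**Conclusion.** The concern holds in a limited, conditional form. As listed, the saliva prevalence-ratio model omits a factor that the article expects to matter. If the enrolment round is included, the year ratio can show a false change while true prevalence is constant.

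Neither direction nor size can be fixed from the article. Across the codings tried, the false ratio runs from 0.83 to 1.25 at an assumed 60%/40%, and from 0.92 to 1.10 at 30%/25%. It is 1.00 throughout if there is no seasonal gap or if enrolment is left out.

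The descriptive primary result, point prevalence for each season and year, is not distorted. The age and housing ratios are little affected because the same children are sampled in every round. The correction is worth making because it is nearly free, but it does not threaten the primary description.

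**What to change.** In the quasi-Poisson model for saliva seropositivity, replace year by sampling round (season within year), or keep year and add season. Form year contrasts within the same season: August against August, March against March. State how year is coded and whether the enrolment round is included.

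Sampling round is the safer choice. Do not give enrolment its own level alongside year where enrolment is the only round in year 1, as with calendar years and wet enrolment: the two terms would then be aliased.

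The cost is one covariate in the model statement and a sentence defining year. No new data or visits are needed.

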Describe epidemiology of symptomatic *Aedes*-transmitted infections in a Cambodian pediatric population	Positive RT-PCR result for diagnosis of dengue, chikungunya, and Zika viruses (or IgM capture ELISAs for dengue as needed)	Dengue is the predominant flavivirus, but other circulating arboviruses complicate the serologic diagnosis of prior immunity and it will be important to characterize this burden given the ease and little cost added to run the multiplex RT-PCR compared to a DENV RT-PCR alone
Establish and characterize spatial relationships between population abundance of *Ae. aegypti* (through entomological indicators), magnitude of human antibody response to *Ae. aegypti* mosquito saliva, and disease development	Geographical information system with all data components (mosquito catch sites, houses, schools) referenced by latitude and longitude in addition to a series of map layers (point maps, smoothed maps) to evaluate relationships between IgG intensity of human antibody response (ΔOD per ELISA) to *Ae. aegypti* salivary homogenate, entomological indices (e.g. House index defined as larvae present per 100 houses surveyed), and disease development	These data and analyses will allow for detailed spatio-temporal analysis of the data at individual, house and community levels. Similar published methods (except different entomological indices) were used for assessment of *Anopheles* salivary protein exposure at the Thai-Burma border for risk of malaria transmission [53]
Characterize temporal dynamics of human antibody reactivity to *Ae. aegypti* salivary gland homogenate	Seroconversion to *Ae. aegypti* salivary homogenate in relationship to season (wet *versus* dry) and collected time-dependent variables defined as mean and maximum rainfall, temperature and humidity	The natural time course of salivary protein exposure, particularly in confirmed arboviral disease settings, has not been well characterized. Retrospective repeat analyses of non-diseased samples have suggested that salivary IgG antibodies may last 30–40 days or possibly up to 4 months [18]. Seasonal variation and climate factors are implicated in both disease transmission and vector abundance [54, 55]. Quantifying vector-host interaction at the individual level in the context of more global factors is necessary to further understanding saliva immunity, disease transmission, and outbreak model prediction

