Characterize the presence and types of alpha-thalassemia variants in the Cambodian population	Presence or absence of alpha thalassemia as determined by genotyping of alpha globin deletions and variants in cohort participants and targeted sequencing of these candidate genes	Dengue-infected patients with alpha thalassemia clinically present differently than patients without erythrocyte variants [49, 50]. In *vitro* studies have also shown that cells derived from thalassemia trait carriers have reduced susceptibility to DENV infection. Describing the presence of alpha-thalassemia in the Cambodian population as well as the associated alpha globin deletions will be important for future studies to investigate the link between alpha thalassemia and arboviral disease development
Characterize pattern of *Aedes* salivary reactivity and cellular immune responses to saliva across baseline, final, acute and convalescent time points of *Aedes*-transmitted disease	Evaluation of the cellular immune response to *Aedes* whole salivary gland homogenate (e.g. assess T-cell activation or cytokine production by vector saliva) in participants at baseline, final study visit, and time points after with RT-PCR-confirmed infection with DENV, CHIKV, or ZIKV	Understanding cellular immunity to *Aedes* saliva will inform vaccine design. An ultimate aim of identifying a small peptide antigen in *Aedes* saliva would be its use as an adjuvant in conjunction with an arboviral-specific antigen for vaccine development

Twice per year, during dry (March) and wet (August) seasons, participants come to their local pagoda, a community temple, to provide blood samples for tests of seroconversion after DENV infection and to characterize their *Aedes* salivary protein seroconversion profiles (Table 2). At any time of year, febrile children are referred to the district hospital where putative cases of febrile *Aedes*-transmitted arbovirus infections can be identified by symptoms (e.g. fever, myalgias, headache, rash). For febrile cases with positive rapid diagnostic tests or for those with a high index of clinical suspicion, confirmatory tests of viral shedding of DENV, CHIKV or ZIKV virus are performed *via* RT-PCR.

**Table 2 Tab2:** Schedule of activities

Procedure	Screen and enroll	Dry ± 28 days	Wet ± 28 days	Dry ± 28 days	Wet ± 28 days	Dry ± 28 days	Wet ± 28 days	Febrile sick visit ± 2 days	Convalescent visit Day 7 ± 2 days	Convalescent visit Day 28 ± 4 days
Informed consent	×									

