### Sample size calculation

There are no published seroprevalence studies exclusively for Cambodian children, but multiple pediatric seroprevalence studies are reported from neighboring Thailand and Malaysia [29–31]. The most recent incidence studies in Cambodia suggest that the most conservative estimate, or the lowest incidence rate, of acute dengue infection in Cambodia as approximately 14 per 1000 person-seasons (range 13.7–58 per 1000 person-seasons in neighboring province to Kampong Speu) [24].

It is difficult to make presumptions regarding the exposed mosquito saliva protein (MSP+) and unexposed mosquito saliva protein (MSP-) populations as the only available retrospective study data from Thailand suggested that seroconversion occurs to major *Ae. aegypti* proteins 0–25% of the time in non-infected hospitalized children *versus* 0–75% in DENV-infected hospitalized children [19]. Therefore, the sample size was primarily determined by the number necessary for DENV seroprevalence. With a sample size of 701 accounting for 10% dropout to yield a total goal enrollment of 771 participants, a simple random sample of a binary response (infected or not) with an exact 95% confidence interval on the true proportion will have an average length of less than or equal to 0.075 regardless of the true rate.

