We will perform regression models (logistic for dichotomy predictors, quasi-Poisson models for incidence rates, linear models or mixed models for continuous predictors), to investigate the effect of environmental and socio-demographic conditions on the prevalence of *Aedes* salivary protein seroconversion (e.g. age, type of housing, number of domestic water containers) and season-specific data such a humidity, temperature and rainfall. All data will be geographically referenced. To evaluate spatial or temporal aggregation of salivary gland seroconversion, space-time scan statistics will be used. Exploratory spatial analyses will look for statistical clustering of disease, of IgG response and of mosquito abundance using both global and local indicators of spatial autocorrelation [33]. Smoothed heat maps will be created using QGIS software (https://www.qgis.org/en/site/). Spatial data will then be used to estimate risk factors for strongly positive antibody response to *Ae. aegypti* saliva and to risk of disease using generalized linear regression or generalized additive models (quasi-Poisson and logistic regression models), where appropriate.

The difference between groups in continuous secondary/exploratory outcomes will be tested by nonparametric Wilcoxon rank sum test, or if inferences on differences in means are desired, using a 2-sample t-test [34]. To test for differences among more than two groups, either a Kruskal-Wallis rank test (for nonparametric inferences) or a one-way ANOVA (for inferences on the means) will be used to test for overall differences. An appropriate data transformation (e.g. log_10_-transformation) may be applied to make inferences on ratios of geometrics means or to better satisfy assumptions of symmetry and homoscedasticity (similar variance).

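### Season-level climate effects on salivary seroconversion rest on six or seven sampling rounds, not on thousands of child results, and the planned regressions state no round-level error term

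*Protocol article*

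**What the plan says.** One secondary objective in Table 1 (Study design and objectives) concerns the temporal dynamics of antibody reactivity to *Ae. aegypti* salivary gland homogenate (SGH). Its endpoint relates seroconversion to season, wet versus dry, and to "collected time-dependent variables defined as mean and maximum rainfall, temperature and humidity".

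The Statistical analysis section plans regressions to study environmental and socio-demographic effects "on the prevalence of *Aedes* salivary protein seroconversion". Age, type of housing and number of water containers are examples of covariates, and the same sentence adds "season-specific data such a humidity, temperature and rainfall". The model types are listed as "logistic for dichotomy predictors, quasi-Poisson models for incidence rates, linear models or mixed models for continuous predictors".

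On timing, the article says "Twice per year, during dry (March) and wet (August) seasons, participants come to their local pagoda". In Table 2, the row "Sera collection for ELISAs" is marked at enrolment and at three dry and three wet visits, each seasonal visit with a window of ±28 days. The remaining marks in that row belong to sick and convalescent visits. SGH seroconversion "is measured repeatedly on subjects over three years during wet and dry season". Table 3 restricts the cohort to children living within about 5.5 km of the referral hospital.

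**The concern.** Weather described at season level, in an area this small, hardly differs between children seen in the same round. It differs between rounds. The information on a climate effect is therefore limited by the number of rounds, however many children are sampled in each.

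The sentence that introduces the climate variables also lists child-level and house-level covariates, so the natural reading is one data row per child per round. In such a fit, anything else that moves SGH prevalence from one round to the next (mosquito abundance, vector control, assay batch, an unusual year) is shared by every child in that round. Without a round-level error term the model treats this shared movement as thousands of independent confirmations and attributes it to whichever climate variable lines up with it. Clustering on the child deals with a different dependence and leaves this one in place.

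What is at stake is the credibility of the climate findings under a named secondary objective.

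**Working it through.** **The article's own figure.** The only sample-size statement is for dengue seroprevalence: "With a sample size of 701 accounting for 10% dropout to yield a total goal enrollment of 771 participants", with an average exact 95% interval length of at most 0.075. At a true proportion of 0.5 the expected Clopper-Pearson length for n = 701 is 0.0753, and n = 706 is the smallest size at or below 0.075. So 701 reproduces to within rounding, and 701 × 1.1 = 771.1 gives 771. No figure is given for the climate regressions.

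**Counts.**
- Rounds: 2 per year × 3 years = 6, or 7 with enrolment.
- Child-round results: 701 × 6 = 4,206 up to 771 × 7 = 5,397.
- Climate summaries: mean and maximum of 3 variables = 6.
- Intercept + 6 summaries = 7 parameters. With one value per round this is not estimable from 6 rounds (rank 6) and is saturated with 7 rounds (0 residual degrees of freedom).
- Adding season gives 8 parameters, more than either number of rounds.
- One climate term with an intercept leaves 6 − 2 = 4 or 7 − 2 = 5 round-level degrees of freedom.

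**False-positive rate for one null climate term.** Assumptions: one weather value per round, unrelated to the round effects; 701 children per round; prevalence about 50%; children independent within a round apart from the shared round effect; between-round standard deviation τ on the logit scale. The documents give no value for τ. At 50% prevalence, τ = 0.1 is about 0.25 × 0.1 = 2.5 percentage points, and τ = 0.3 about 7.5.

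Approximation by hand: the sampling variance of a round's logit is 1/(701 × 0.25) = 0.0057. Ignoring the round understates the variance by the factor f = 1 + τ²/0.0057, and the true level is 2[1 − Φ(1.96/√f)].
- τ = 0.1: f = 2.75, 1.96/1.66 = 1.18, level about 24%.
- τ = 0.2: f = 8.0, 1.96/2.83 = 0.69, level about 49%.
- τ = 0.3: f = 16.8, 1.96/4.10 = 0.48, level about 63%.

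Simulation, 1,000 data sets per setting, nominal 5%:

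| τ | Child-level logistic, 6 rounds | Child-level logistic, 7 rounds | Round-level t-test, 6 / 7 rounds |
|---|---|---|---|
| 0 | 5.0% | 5.3% | 4.7% / 5.4% |
| 0.1 | 21.1% | 24.8% | 4.3% / 6.1% |
| 0.2 | 48.1% | 46.9% | 4.7% / 4.7% |
| 0.3 | 64.4% | 64.0% | 6.1% / 5.1% |
| 0.5 | 77.6% | 74.7% | 4.8% / 4.2% |

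A separate simulation with 300 data sets per setting and 7 rounds gave 25%, 49% and 65% for τ = 0.1, 0.2 and 0.3. The hand calculation and both simulations agree.

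**The case against.** The strongest reply is that the article does not fix the analysis criticised here. It specifies no climate test. It names mixed models. It already commits to presenting SGH prevalence for each season of each year, which is the round-level summary one would want. It does not give the source or resolution of the weather data. A random effect for round could reasonably be left to a fuller plan. Visit windows of ±28 days and a three-month enrolment period would also allow weather linked to the visit date. And the rates above depend on an assumed τ: at zero there is no inflation.

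Much of this stands, and it rules out several stronger readings that a reader might infer:
- *More climate terms than rounds.* Not so: there are six summaries against six or seven rounds. Only the parameter count with intercept and season exceeds both.
- *An unidentifiable model is planned.* The article does not say that all terms enter one model. Fitting them singly is consistent with the text.
- *The p-values would mean nothing.* Too strong. A child-level fit would be anticonservative, and a round-level test on the same data holds its level.
- *Rainfall forces a linear model on a binary outcome.* That is the literal wording, but it is probably a slip of predictors for outcomes. The same list contains incidence rates, which are an outcome, and elsewhere in the section logistic and quasi-Poisson models are used for seropositivity.
- *The coefficients will drive outbreak prediction.* Table 1 mentions prediction only as general motivation.

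The reply does not remove the core. Mixed models are listed only for continuous predictors and without a grouping level. Visit-date weather would add only a few correlated values, still shared by children sampled together. Zero between-round variation is hard to defend when the article justifies three years of follow-up by large year-to-year variability in transmission, although that remark concerns disease rather than SGH antibodies.

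**Conclusion.** The point holds in a limited form. Season-level climate effects rest on six or seven rounds, and the stated regressions include no term for variation between rounds. Fitted at child level, a single null climate term would be declared significant in roughly a quarter to two thirds of studies for τ between 0.1 and 0.3, against 5% nominal. This depends on weather being essentially common to a round, on a child-level fit without a round term, and on an assumed τ. Season and all six summaries could not be estimated jointly from so few rounds, should anyone try. The wording on model choice is an error as written, most likely editorial, and does not by itself invalidate any inference. The matter concerns a secondary objective; the primary endpoints and the sample size are untouched.

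**What to change.** 1. For climate, name one summary in advance, for example rainfall over a stated period before sampling that suits the antibody persistence cited in Table 1. Relate the round-specific SGH prevalences to it, shown as a plot. If a child-level model is preferred, include a random effect for round, a single climate term and round-level degrees of freedom.
2. Report the climate result as descriptive, and state that wet/dry season and weather largely share the same contrast.
3. Reword the list of models so that the choice follows the outcome: a logit or log link for binary SGH status, linear or mixed models for optical density.

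The cost is wording only, with no new data, visits or participants. The downside is that the climate result becomes descriptive, with 4 or 5 residual degrees of freedom.
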